### Primary health outcomes

3.1

#### Complete blood count

3.1.1

After fasting for at least 8 h, blood samples were collected into EDTA anticoagulant tubes, and blood collection time and volume should be recorded. Then, hematological parameters were analyzed by an automated blood cell analyzer (SYSMEX, XS-1000, Japan) (36).

### Secondary health outcomes

3.2

#### Thyroid hormones

3.2.1

Fasting venous blood samples of radiation workers were collected in the morning and were placed in a centrifuge tube containing separation gel, centrifuged at 3000 rpm for 10 min, then collected serum samples were added in labeled test tubes, and test triiodothyronine (T3), thyroxine (T4), and thyroid-stimulating hormone (TSH) with automatic chemical immunoanalyzer (MAJLUMI4000PLUS, China), which are frequently used to evaluate thyroid function (41, 59).

#### Liver and kidney function tests

3.2.2

Collected blood was centrifuged, following which the relevant biochemical blood index was measured using an automatic biochemical analyzer (Beckman, AU680, United States) (60), including the fasting blood glucose (FBG), creatinine, uric acid, blood urea nitrogen (BUN), alanine transaminase (ALT), gamma-glutamyl transferase (GGT), total bilirubin, direct bilirubin, alkaline phosphatase (ALP), aspartate transaminase (AST), etc.

#### Chromosome aberration analysis

3.2.3

Chromosome aberrations are a biological dosimeter that can evaluate ionizing radiation injury in genetics (61). The process reference to the national standard of GBZ/T 248–2014 (62). Analyze the chromosome karyotype and interpret the test results as follows: (1)The normal reference range for the acentric fragment aberration rate is 0–3%; values exceeding 3% are considered abnormal (62) (2). A double centromere, centromeric ring, or stable chromosome aberration rate of ≥1% is deemed abnormal (62, 63) (3). Abnormal results may warrant retesting within 3–6 months (62).

#### The micronucleus test

3.2.4

The micronucleus test (MNT) has been used as a screening method to demonstrate the cytoplasm’s aberrant chromosomal material (micronuclei). This test facilitates the rapid and automated detection of chromosome damage caused by radiation and indicates chromosomal instability (64). The process mainly references the national standard of GBZ/T 328–2023 (65). Finally, interpret the test results as follows: (1) The normal reference range for the micronucleus rate using the conventional culture method is 0–6%, while for the cytokinesis-block micronucleus assay, it ranges from 0 to 30% (63, 65). (2) If the test results exceed the normal reference range, chromosomal aberrations in peripheral blood lymphocytes should be further evaluated (65).

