### Inclusion and exclusion criteria

2.2

Included in the study will be radiation workers who are: (1) consistently wear dose dosimeters; (2) regular occupational health examination at the Chongqing Center for Disease Control and Prevention (CDC); (3) over 18 years old; (4) no communication barriers (34, 36). Excluded from the study will be those who are with a history of chromosomal aberrations, micronucleus abnormalities, peripheral blood abnormalities and blood-related diseases, abnormal liver and kidney function, cancer, history of abnormal thyroid hormones and thyroid-related diseases, and cataract and glaucoma (34, 36).

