
### Baseline information

2.6

The basic characteristics of the study population in 2016 are presented in Table 1.

**Table 1 tab1:** Characteristics and health outcomes of radiation workers in Chongqing, 2016.

	Mean ± SD / M[IQR]/ n (%)
Age	37.00 [31.25, 47.00]
Gender *n* (%)	
Male	30 (60)
Female	20 (40)
Education *n* (%)	
Associate degree or below	7 (14)
Undergraduate	37 (74)
Master’s degree	6 (12)
Marital status *n* (%)	
Unmarried	18 (36)
Married	32 (64)
White blood cells (10^9^/L)	5.72 ± 1.46
Red blood cells (10^12^/L)	4.88 ± 0.65
Hemoglobin (g/L)	142.90 ± 21.40
Platelets (10^9^/L)	214.32 ± 58.01
Hematocrit (%)	42.77 ± 5.63
Mean corpuscular hemoglobin (pg)	30.20 [28.65, 30.98]
Alanine transaminase (U/L)	19.75 [15.90, 29.38]
Blood urea nitrogen (mmol/L)	5.12 ± 1.35
Creatinine (μmol/L)	58.05 [51.95, 72.90]
Uric acid (umol/L)	235.51 ± 51.81
Gamma-glutamyl transferase (U/L)	17.00 [13.00, 26.50]
Total bilirubin (μmol/L)	10.02 [6.93, 12.97]
Direct bilirubin (μmol/L)	3.25 [2.42, 4.18]
Alkaline phosphatase (U/L)	74.50 [57.25, 93.50]
Fasting blood glucose (mmol/L)	4.70 [4.40, 5.10]
Proteinuria *n* (%)	
Positive	3 (6)
Hematuria *n* (%)	
Positive	5 (10)
Audiometry *n* (%)	
>25 dB	0 (0)
Triiodothyronine (T3)	1.29 [1.12, 1.58]
Thyroxine (T4)	105.92 ± 16.59
Thyroid-stimulating hormone (TSH)	1.44 [0.80, 1.78]
Lens opacity *n* (%)	
Abnormal	2(4)
Dermatological assessments *n* (%)	
Abnormal	0 (0)
Micronucleus rate *n* (%)	
2‰	1 (2)
Chromosomal aberrations rate *n* (%)	
1%	1 (2)

IQR, interquartile range; SD, standard deviation.

According to the national standard GBZ 128–2019 (42), the target population includes medical radiation workers, industrial radiation workers, and others, excluding veterinary medicine. The distribution of workers across these three occupational categories in 2016–2020 is presented in Figure 1.

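### Micronucleus reference limits are printed in percent while Table 1 records the rate in per mille: a tenfold unit slip is likely and must be checked against the cited standard

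*Protocol article*

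**What the plan says.** Section 3.2.4, on the micronucleus test (a secondary health outcome), gives one upper limit for each of two assays. For the first, "The normal reference range for the micronucleus rate using the conventional culture method is 0–6"%. For the second, "while for the cytokinesis-block micronucleus assay, it ranges from 0 to 30"%. The same section attaches an action to the range: "If the test results exceed the normal reference range, chromosomal aberrations in peripheral blood lymphocytes should be further evaluated".

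Table 1 in section 2.6, titled "Characteristics and health outcomes of radiation workers in Chongqing, 2016", also carries a micronucleus rate. Its only listed category is 2‰, in 1 worker (2%). The row directly below gives the chromosome aberration rate, with a listed category of 1%.

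Section 2.2 excludes workers with a "history of chromosomal aberrations, micronucleus abnormalities, peripheral blood abnormalities and blood-related diseases", among other conditions. It gives no number for what counts as a micronucleus abnormality and does not point to section 3.2.4. No micronucleus limit in per mille appears anywhere in the article.

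**The concern.** One quantity appears in two units that differ by a factor of ten, and the unit of the decision limit is not the unit of the recorded data. The percent limits also look very wide beside the one rate that the article reports.

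The neighbouring test makes a mere choice of notation less likely. For chromosome aberrations, Table 1 uses percent and so do the cut-offs in section 3.2.3 (0–3% for acentric fragments; 1% or more for the other listed types). For micronuclei, Table 1 uses ‰ one row above a % entry, so the ‰ sign there looks deliberate, and section 3.2.4 is the place that departs from it.

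At stake is how results are read. The range decides which micronucleus results count as abnormal and which lead to chromosome aberration evaluation. The data come from routine examinations in a study planned for 2024 to 2044, so a wrong unit in the rule could persist for a long time.

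**Working it through.** The limits are taken from cited standards and are not derived in the article, so there is no calculation of the plan's own to reproduce. The check is a unit conversion and a comparison.

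**Inputs**
- Upper limit, conventional culture: 6% as printed (section 3.2.4).
- Upper limit, cytokinesis-block: 30% as printed (section 3.2.4).
- Listed rate: 2‰, in 1 worker (Table 1).
- Table 1 denominator: 30 men + 20 women = 50, and 1/50 = 2%, which agrees with the printed percentage.

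**Conversion** (1% = 10‰)
- 6% = 6 × 10 = 60 per 1,000 cells.
- 30% = 30 × 10 = 300 per 1,000 cells.
- 2‰ = 2 per 1,000 cells = 0.2%.

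**Limit divided by the listed rate**

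| Assay | Unit assumed for the limit | Limit per 1,000 cells | Ratio to 2 per 1,000 | Is 2‰ above the limit? |
|---|---|---|---|---|
| Conventional | % (as printed) | 60 | 60/2 = 30 | No |
| Conventional | ‰ (same digits) | 6 | 6/2 = 3 | No |
| Cytokinesis-block | % (as printed) | 300 | 300/2 = 150 | No |
| Cytokinesis-block | ‰ (same digits) | 30 | 30/2 = 15 | No |

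Table 1 does not say which assay produced the 2‰, so both pairs of ratios are shown.

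**Where the unit would matter.** The two readings classify a result differently only when it lies above the per-mille limit and at or below the percent limit. That band runs from above 6 up to 60 per 1,000 cells for conventional culture, and from above 30 up to 300 per 1,000 for the cytokinesis-block assay. The listed value of 2 per 1,000 lies below both bands, so nothing reported in the article changes class.

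**The case against.** The strongest reply is that the text contains no contradiction. The article states one set of limits. Table 1 gives an observed value and not a limit, and 0.2% lies comfortably inside 0–6%. Two units for one measure may be untidy without being wrong. The plausibility argument rests on one worker out of 50, with no value shown for the other 49, no assay named, and data from 2016 that predate the 2023 standard followed in section 3.2.4. All of this stands. It rules out saying that the article holds two thresholds in tenfold conflict, or that the limit is known to be wrong.

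A reader might also infer three stronger consequences that the document does not support:
- *That the limit defines an exclusion criterion.* Section 2.2 names "micronucleus abnormalities" only as a history, without a cut-off and without reference to section 3.2.4. The link is an inference.
- *That a binomial outcome would have no events.* Section 2.5 assigns Gaussian, Poisson or binomial models by type of outcome and does not say that the micronucleus rate will be dichotomised. No distribution of rates is given from which to count events.
- *That abnormal workers are already being missed.* The one listed value is normal under either unit.

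The objection does not remove the mismatch itself. Both signs are legible in the text, the neighbouring test uses matching units in the table and in its rule, and the article prints an explicit limit with an action attached. This is a stated figure and not a detail left to a fuller document.

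**Conclusion.** The concern holds as a unit inconsistency between section 3.2.4 and Table 1, with a likely but unconfirmed tenfold slip in a stated decision limit. If the slip is real, the printed limits of 60 and 300 per 1,000 cells are ten times wider than intended. Applied literally, they would then flag few or no results, both in interpreting this secondary outcome and in triggering chromosome aberration evaluation.

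This rests on two assumptions: that Table 1 is in the intended unit, and that the digits 6 and 30 are right and only the sign is wrong. Neither can be settled from the article; the cited standard must decide.

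The reach is limited. The primary outcome (complete blood count), the sample size (based on white cell count) and every entry in Table 1 are unaffected. Severity is moderate, not must-fix, and confidence is moderate.

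**What to change.** Check the ranges in section 3.2.4 and the rate in Table 1 against the national standard that section 3.2.4 cites, and reconcile the two places. Then state the reference ranges and the recorded rates in one unit, for example micronuclei per 1,000 cells, and confirm that results are recorded in that unit. Do this before any result is classified. If the entry criterion in section 2.2 is meant to use the same range, say so there.

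Optionally, analyse the micronucleus count under the Poisson model already planned for count outcomes, with the number of scored cells as offset, so that the analysis does not depend on the cut-off.

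The cost is a check of one source, a correction of units in one or two places, and a check of data-entry units. No new data are needed.

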#### Ophthalmic examinations

3.2.5

Routine ophthalmic examination includes visual acuity, color vision, vitreous, fundus, and a slit-lamp lens examination to investigate lens opacities, visual acuity (VA) in each eye was tested by using Snellen and Jaeger charts (66). Pupillary dilation to ≥6 mm is induced with 1% tropicamide, and digital photographs of the lens were obtained by using the slit lamp (SLM-KD4, China) (66), providing detailed information on the location and degree of opacity and confirming the cataract type (67).

#### Urinalysis

3.2.6

Urinalysis was performed using an automated urine analyzer (URIT-1600, Guilin, China) for chemical and sediment analyses. Urine sediments were obtained by centrifugation at 500× g for 15 min, a drop of pellets was then placed on a glass slide, covered with a cover slip, and observed under a light microscope, proteinuria was evaluated semi-quantitative (+−/+/++/+++), and hematuria is defined as elevated urine erythrocyte quantification (>17/μL), as well as positive in semi-quantitative urinalysis (+−/+/++/+++) (68).

#### Dermatological assessments

3.2.7

Radiation-induced skin injuries can be classified into acute or chronic injuries (69), and the grading criteria refer to GBZ-106-2020 (70). Acute injuries are characterized by symptoms such as erythema, depilation, burning sensation, numbness, itching, edema, and tingling. In contrast, chronic injuries manifest as skin pigmentation or loss, rough and gray nails, skin hyperkeratosis, chapping or atrophic thinning, telangiectasia, nail thickening and deformation, necrotic ulcer, etc. (70). The diagnosis and evaluation of radiation skin injuries are based on these methods: medical history and health examinations, including scenario details, dermatological assessments, timing and duration of signs and symptoms, digital color photographs, etc. (71).

#### Audiometry

3.2.8

Hearing of radiation workers was evaluated through bilateral otoscopic (ITERA, Denmark) examinations conducted in a quiet, soundproof room. Hearing thresholds will be evaluated at 0.5, 1, 2, and 4 kHz frequencies to assess the degree of hearing loss, Hearing loss and its severity were assessed using pure tone threshold averages in the better ear. A pure-tone average exceeding 25 dB in the better ear indicates hearing loss, which is categorized as follows: slight hearing loss (>25 and ≤ 40 dB), moderate hearing loss (>40 and ≤ 60 dB), and severe hearing loss (>60 dB) (1, 2).

## Discussion

4

This article outlines the study protocol for investigating occupational exposure among radiation workers in Chongqing, providing valuable insights and methodological strategies for cohort studies in the region. Despite the increasing awareness of chronic low-dose ionizing radiation exposure, the exposure-lag response associations with various adverse health outcomes remain underexplored, highlighting the need for further research in this area.

Some progress in the cross-sectional survey has been made in the occupational investigation of radiation workers with different health outcomes in China. Regarding the effects of occupational radiation exposure on the complete blood count, Zhang et al. (3) noted that low-dose ionizing radiation could increase the detection rate of abnormal white blood cells in radiation workers, yet no significant effect on hemoglobin and platelets. However, the influencing factors such as years of service and type of work were not further analyzed, which were closely related to the abnormal health outcome (4). Wang et al. showed that the occupational population had a higher risk of white blood cell and platelet counts, while no significant effect was observed on red blood cell counts (4). The cross-sectional survey design made it impossible to monitor the progression of health outcomes over an extended period. In contrast, a cohort study design incorporating longitudinal data enables the evaluation of temporal effects on health outcomes, facilitating the investigation of both long-term cumulative exposure-response relationships and exposure-lag-response dynamics.

Several cohort studies on occupational radiation exposure have been conducted in China, primarily examining outcomes such as cancer incidence and mortality (13, 72), changes in thyroid hormones (41) and complete blood count (73), liver damage (74), cataracts (66). A three-year cohort study showed that long-term low-dose radiation exposure was a risk factor for liver injury (74). In addition, a prospective cohort study explored the effects of occupational radiation exposure on platelets (54). Still, both studies exhibited certain limitations. Specifically, individual dose monitoring data were absent for previous years, and the cumulative radiation dose of the radiographers, as assessed using the job-exposure matrix (JEM) may have introduced measurement bias. Additionally, the radiation dose estimates were uncertain (54, 74). To further elucidate the health effects of occupational radiation exposure, two cohort studies were conducted over a five-year period, Liu et al. (54) performed a cohort involving 1265 medical workers exposed to low-dose ionizing radiation over the same duration. Their findings identified a cumulative exposure-response relationship, with an initial increase in platelet count followed by a subsequent decline (54). Additionally, a dose–response relationship was observed, whereby changes in platelet count were directly correlated with the cumulative dose of radiation received. Conversely, Wang et al. (73) found no significant differences in blood cell counts among 375 medical radiation workers engaged in different types of work. No statistical correlation has been found between the long-term cumulative exposure dose and the platelet count for a five-year period (73). The inconsistency in previous research findings may be attributed to short follow-up durations, limited cohort sizes, and a lack of focus on exposure-lag responses. These cohort studies primarily focus on the long-term cumulative exposure-response relationships, while overlooking the exposure-lag-response, which represents the complex interplay between health outcomes and the timing, duration, and intensity of exposure. This concept acknowledges that health effects from exposure may be delayed, with the risk of outcomes depending on both the intensity and timing of previous exposures.

To address these limitations, we have reviewed the characteristics of prior cohorts and are planning to establish a long-term, enough sample size, prospective cohort study in Chongqing to investigate the exposure-lag response associations and long-term cumulative exposure-response relationships between chronic low-dose ionizing radiation exposure and various adverse health outcomes. Notably, the average annual effective dose of radiation workers monitored in Chongqing from 2016 to 2020 remained below the national individual dose limit and demonstrated an overall downward trend (25, 26, 56).

This study has certain limitations. Data on the physical activity of radiation workers were not collected, which is a recognized risk factor for ocular trauma. Additionally, information on individual ultraviolet (UV) exposure, another significant factor when assessing cataract risk, was not included.

In summary, this study aims to evaluate the health effects of low-dose ionizing radiation exposure among radiation workers in Chongqing. Our study will provide more information on health outcomes and enhance the understanding of work practices and the exposure-lag response association between occupational radiation exposure and the health of radiation workers. It is recommended to further expand the sample size, extend the follow-up time, adopt more advanced statistical methods and improve the dosimetry method in the future, providing a reference for subsequent studies.
